### Sample size

The sample size calculation is based on the primary outcome of OSFD within the first 14 days. Assuming the HDIVC group would gain 2 additional OSFD days compared to the control group (SD 5 days), with a two-sided *α* of 0.05 and power of 0.80, the initial calculation using the formula for two independent sample means required 98 patients per group. To account for non-normal distribution of OSFD, the Pitman asymptotic relative efficiency correction expanded the sample by 15% to 113 per group. Allowing for a 5% dropout rate, the final sample is 238 patients (119 per group). The study plans to recruit 10 patients per month over 24 months. Ethical approval has been gained in participating centers. Centralized online training has been completed to ensure protocol adherence. As of May 30, 2026, the lead center has recruited 34 patients. Participating centers are being activated, which will increase recruitment capacity.

### Randomization and blinding

Participants will be strictly enrolled based on predefined eligibility criteria. Stratified block randomization will be employed by each research center. Patients will be allocated to either the HDIVC group or control group, with allocation concealment maintained throughout. Randomization numbers will be generated by statisticians using SAS 9.4 software, employing block randomization within each stratum to ensure balanced group assignment. Expansion of the sample size may be considered if necessary.

Stratification is performed at three levels: (1) participating center (8 centers), and (2) etiology, categorized as biliary, hypertriglyceridemic, alcoholic or other. Due to our rigorous inclusion criteria, all enrolled patients are diagnosed with SAP. We will not proceed stratification by disease severity. The randomization sequence is generated independently for each stratum combination (8 × 4 = 32 strata) by an independent statistician using SAS 9.4, employing variable block sizes of 4 and 6 (randomly alternated) to ensure allocation concealment and balance within each stratum.

To ensure blinding, study medications—either 50 mL vitamin C solution or matching placebo (0.9% normal saline)—will be prepared in identical, opaque, light-proof containers by UDPN according to the randomization list. Both groups will receive equal volumes (50 mL) via identical administration protocols using the standardized micropump (2 g/h). Crucially, the administration through a central vein minimizes potential sensory cues (such as infusion site irritation) that could arise from pH differences, thereby maintaining the blind for participants, clinical staff, and data analysts. All centers will follow this standardized protocol after thorough training and the study medicine is provided by one center to avoid bias.

The data management and analysis will implement a two-stage unblinding process. After all data have been locked following blinded data verification, the group assignments for each participant will be disclosed for statistical analysis. When the statistical analysis completes, the specific group assignments (intervention group or control group) will be disclosed to assess the study outcomes.

During the treatment period, if complications such as urinary crystals or unexplained acute kidney injury (meeting KDIGO guidelines) occur, emergency unblinding will be performed in accordance with GCP procedures. The attending physician will immediately notify both the site principal investigator and the study-wide principal investigator, who will jointly evaluate the event and determine appropriate clinical management. All such events will be documented and reported to the institutional review board as required.

To reduce the risk of unblinding from pronounced clinical responses, several strategies have been implemented. First, the initiation, titration, and withdrawal of life-sustaining therapies (vasopressors, mechanical ventilation, and CRRT) are protocol-driven. Bedside clinicians follow objective physiological targets and international guidelines rather than subjective judgment. Second, the primary outcome (OSFD within the first 14 days) is a definitive, objective outcome not subject to observer bias. Third, clinical data extraction and calculation of secondary outcomes (SOFA and modified Marshall scores) are performed by independent, blinded research personnel not involved in daily patient management. Investigators will monitor and record events that could lead to unblinding, including unexplained severe AKI or suspected oxalate nephropathy, and spurious glucose readings or glucometer errors.

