### Secondary outcome

The secondary outcomes are: (1) ICU all-cause mortality, defined as death from any cause from randomization to ICU discharge or transfer. (2) Early SAP inflammatory markers, including C-reactive protein and cytokines IL-6, IL-1, and IL-10. (3) Organ function scores, including SOFA and modified Marshall scores. (4) Fluid retention. (5) Disease severity scores, including APACHE II and BISAP scores. (6) Pancreatic necrosis measured by CTSI scores. (7) Other prognostic indicators including the incidence of infected pancreatic necrosis, ICU length of stay, and hospitalization costs. (8) Plasma vitamin C concentrations before and after treatment. (9) Adverse events related to vitamin C. (10) Gut microbiota composition.

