#### AEs include

(1) presence of urinary crystals.(2) occurrence of acute kidney injury (AKI) as defined by KDIGO criteria.(3) clinical or laboratory signs of unexpected hemolytic anemia (e.g., sudden hemoglobin drop combined with elevated indirect bilirubin), specifically to monitor for undetected G6PD deficiency.

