#### Treatment discontinuation criteria

Study drug infusion must be discontinued immediately for any of the following events. Emergency unblinding may be performed if deemed necessary by the attending physician:

(1) new-onset AKI meeting KDIGO Stage 2 or 3 (serum creatinine ≥ 2.0 × baseline or urine output < 0.5 mL/kg/h for ≥ 12 h) judged as potentially related to vitamin C-associated oxalate nephropathy.(2) microscopic urinalysis showing abundant calcium oxalate crystals (≥50 per high-power field) with acute creatinine rise.(3) clinical or laboratory evidence of hemolytic anemia (sudden hemoglobin drop, elevated indirect bilirubin, hemoglobinuria).(4) confirmed hypoglycemia (<3.9 mmol/L) after excluding glucometer interference by venous blood gas confirmation.(5) any SAE judged as possibly or definitely related to the study drug.

Both AEs and SAEs will be evaluated at 8:00 a.m. every day. Investigators are required to promptly assess the aforementioned adverse events. If the investigator determines that an abnormal laboratory result is clinically significant and not part of the clinical condition, it should be recorded as an adverse event and report to the PI of each research site. Once confirmed, the intervention should be discontinued immediately and proper medication should be taken.

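### Harm outcome (9) counts events related to vitamin C, but the plan allows relatedness to be judged after a mandatory code break and names no blinded causality assessor

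*Protocol article*

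**What the plan says.** **Code break.** Under Randomization and blinding, the protocol article says that during treatment "if complications such as urinary crystals or unexplained acute kidney injury (meeting KDIGO guidelines) occur, emergency unblinding will be performed". The attending physician then notifies the site and study-wide principal investigators, "who will jointly evaluate the event and determine appropriate clinical management".

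**A second unblinding rule.** Treatment discontinuation criteria opens its list of stopping events with "Emergency unblinding may be performed if deemed necessary by the attending physician". Two of those events contain a relatedness judgement: new AKI "judged as potentially related to vitamin C-associated oxalate nephropathy", and "any SAE judged as possibly or definitely related to the study drug". The blind status of the person judging is not given.

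**Harm outcome.** Item (9) under Secondary outcome is "Adverse events related to vitamin C". Neither the assessor nor the method of deciding relatedness is stated.

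**Event list.** The adverse event list includes "presence of urinary crystals" and "occurrence of acute kidney injury (AKI) as defined by KDIGO criteria", with signs of unexpected haemolytic anaemia as the third item. None of the three carries a relatedness condition.

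**Blinded personnel.** Randomization and blinding assigns independent blinded staff to data extraction and to the organ scores. Causality of adverse events is not among their tasks.

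**The concern.** An event in a patient known to be on saline can hardly be called related to vitamin C. The same event in a patient known to be on HDIVC can. If relatedness is decided with the code open, the attribution rule differs between arms, and outcome (9) can show an HDIVC excess when true event rates are equal.

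The judgement is discretionary in this population. Every participant has persistent organ failure at entry, so new AKI could plausibly be put down either to the disease or to the drug. The triggers that force the code break are also two of the three named adverse events.

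A later analysis plan cannot repair this. A blinded judgement that was not recorded before the code was opened cannot be recovered from the person who opened it. The lead centre had already recruited 34 patients when the article was written.

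**Working it through.** **1. Order of events in the text**

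| Place | Unblinding | Relatedness |
|---|---|---|
| Randomization and blinding | Mandatory for crystals or unexplained KDIGO AKI | Not mentioned; the investigators' evaluation is described after the code break |
| Treatment discontinuation criteria | At the physician's discretion | Part of two stopping criteria; timing and blinding not stated |
| Secondary outcome, item (9) | Not mentioned | Defines the outcome |
| Adverse event list | Not mentioned | Not required |

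Nothing here requires relatedness to be judged after the code break, and nothing prevents it. The two unblinding rules also differ, so sites could differ in how often the code is open when an event is assessed.

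**2. Sample size, used only for the number per arm**

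Inputs from the Sample size section: difference 2 days, SD 5, two-sided alpha 0.05, power 0.80.

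- n = 2 × [5 × (1.960 + 0.842) / 2]² = 98.1 (stated: 98)
- 98 × 1.15 = 112.7, rounded up to 113
- 113 / 0.95 = 118.9, rounded up to 119 per arm

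The stated figures reproduce and are not at issue.

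**3. Illustration of the possible bias**

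The article gives no event or attribution rates, so these are assumptions:

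- p: true event risk, equal in both arms (10%, 20%, 40%)
- q: share of events called related in the HDIVC arm (25%, 50%)
- r: control attribution relative to HDIVC (1 if blinded; 0.5; 0 if no control event is ever called related)

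The risk of a related event is p × q on HDIVC and r × p × q on control. For example, p = 0.20 and q = 0.50 give 119 × 0.20 × 0.50 = 11.9 expected on HDIVC. On control the figure is 11.9, 6.0 or 0 for r = 1, 0.5 or 0. The chance that a two-sided Fisher test gives p<0.05 was found by exact enumeration of two binomials with 119 per arm. The plan does not specify this test; it serves only as a yardstick.

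| p | q | Expected related, HDIVC | r = 1 | r = 0.5 | r = 0 |
|---|---|---|---|---|---|
| 0.10 | 0.25 | 3.0 | 0.011 | 0.022 | 0.079 |
| 0.10 | 0.50 | 6.0 | 0.021 | 0.086 | 0.55 |
| 0.20 | 0.25 | 6.0 | 0.021 | 0.086 | 0.55 |
| 0.20 | 0.50 | 11.9 | 0.028 | 0.22 | 0.983 |
| 0.40 | 0.25 | 11.9 | 0.028 | 0.22 | 0.983 |
| 0.40 | 0.50 | 23.8 | 0.035 | 0.513 | 1.00 |

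A split of 5 v 0 gives p = 0.060, and 6 v 0 gives p = 0.029.

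**4. The same events counted whatever their attribution**

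With p = 0.10, 0.20 and 0.40 in both arms, the chance of p<0.05 is 0.028, 0.035 and 0.039. This count carries no attribution bias.

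**The case against.** A reader might infer that related events can be counted only in the HDIVC arm, so that the harm comparison is biased by construction. The documents do not support that.

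- The sentence on the principal investigators speaks of evaluating the event and managing the patient, not of causality. Reading sentence order as time order is an inference.
- The stopping criteria build a relatedness judgement into the trigger and leave unblinding optional. That wording fits a judgement made before any code break.
- Crystals, KDIGO AKI and haemolytic anaemia are adverse events in either arm whatever their cause, so a comparison free of attribution remains available. Outcome (9) could even be read as loose shorthand for that list.
- No between-arm test of outcome (9) is specified. It is not one of the four named steps in the testing hierarchy, and its status among the remaining secondary outcomes is unclear.

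A reader might also infer that the DMC would act on a count of related serious events. The relatedness wording is a rule for stopping one patient's infusion, and nothing shown makes it a DMC trigger.

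It can further be said that causality forms belong in a full protocol that is not shown. That is fair for the forms. But the article itself fixes both the mandatory code break and an outcome defined by attribution, and together these leave the gap open. The event list does not fully close it either. Abnormal laboratory results are recorded as adverse events only if the investigator considers them clinically significant and not explained by the patient's condition, and that judgement too could be made with the code open.

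**Conclusion.** The point holds as a weakness that the plan permits, not as a demonstrated bias. The code break is mandatory for crystals and unexplained KDIGO AKI, an evaluation is described after it, outcome (9) is defined by attribution, and no blinded causality assessor is named. If relatedness is judged with the arm known, the error would lower the control count and so tend to exaggerate harm from HDIVC.

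The size cannot be determined from the documents. Over the assumed grid, with no true difference, the illustrative false-signal rate is about 8-100% if no control event is called related, 2-51% at half the HDIVC attribution, and 1-3.5% with blinded attribution. The top of the first range is an extreme case and should not be read as a forecast. A change is worth making because it is cheap and the blinded judgement cannot be recovered later.

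**What to change.** - **Redefine outcome (9)** as the incidence of urinary crystals, KDIGO AKI and haemolytic anaemia by randomised arm, regardless of attribution. Give relatedness as a supportive listing.
- **Protect the relatedness judgement.** Have it entered in the eCRF before any code break where feasible. Otherwise have it made by existing staff who have not seen the code. Use only this blinded judgement in the analysis.
- **Reconcile the two unblinding rules.** The sponsor must bring the mandatory wording in Randomization and blinding into line with the discretionary wording in Treatment discontinuation criteria. No view is taken here on which clinical rule is right.

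The first two changes do not affect when a patient may be unblinded or how an event is treated. They cost a reworded outcome, a sentence on the order of recording and a short eCRF entry, with no new patients, visits or procedures. The drawback is that the all-cause count will include disease-related AKI in both arms, which may dilute a true drug effect on that component.

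### Emergency unblinding is mandatory in one section and discretionary in another for overlapping renal events, and the mandatory rule has no severity threshold

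*Protocol article*

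**What the plan says.** Two sections of the protocol article govern unblinding after a suspected renal complication of the study drug.

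- **Randomization and blinding.** During treatment, "if complications such as urinary crystals or unexplained acute kidney injury (meeting KDIGO guidelines) occur, emergency unblinding will be performed in accordance with GCP procedures". Notice then goes from the attending physician to the site and overall principal investigators, "who will jointly evaluate the event and determine appropriate clinical management". The event is documented and reported to the review board.
- **Treatment discontinuation criteria.** Five listed events require the infusion to stop at once, and for these "Emergency unblinding may be performed if deemed necessary by the attending physician". Two of the five are renal. One is "new-onset AKI meeting KDIGO Stage 2 or 3", where the event is judged possibly due to vitamin C oxalate nephropathy. The other is urine microscopy with "abundant calcium oxalate crystals (≥50 per high-power field) with acute creatinine rise".

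The adverse event list (AEs include) names "presence of urinary crystals", again without a count. Randomization and blinding also states, as a safeguard against the effects of unblinding, that "the initiation, titration, and withdrawal of life-sustaining therapies (vasopressors, mechanical ventilation, and CRRT) are protocol-driven".

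**The concern.** An investigator facing a renal event needs one answer to the question of whether the code is broken. Here the answer depends on which section is read. The stricter instruction is attached to the looser trigger: crystals of any number fall under the mandatory rule, whereas heavy crystalluria with a creatinine rise also falls under a rule that allows the blind to be kept.

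Two things are at stake. First, the protocol itself treats crystals and oxalate nephropathy as effects to watch for with vitamin C, so automatic code-breaks for crystals would plausibly fall more heavily on the HDIVC arm. Blinding would then be lost unequally. Second, the primary outcome counts days without vasoactive drugs, ventilation or renal replacement. It therefore depends on decisions to give support, and those who manage a renal event may learn the allocation. Centers that follow different sections would also unblind under different rules.

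**Working it through.** No figure in the plan underlies this point, so the check is to apply both rules to the same patients.

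1. **At least 50 oxalate crystals per high-power field with an acute creatinine rise.** Randomization and blinding: crystals are present, so the code is broken. Treatment discontinuation criteria: the drug stops, and the code is broken only if the attending physician thinks it necessary. Both rules apply and they differ. Breaking the code satisfies both, but then the discretion granted in the second section is empty. Keeping the blind satisfies only the second.
2. **A few crystals, stable creatinine.** Randomization and blinding, read literally: the code is broken if the finding counts as a complication. Treatment discontinuation criteria: the crystal criterion is not met, so its unblinding provision is not reached. This case shows how wide the mandatory trigger is; it is not itself a contradiction.
3. **Unexplained KDIGO stage 1 AKI.** Randomization and blinding: the code is broken, since no stage is set. Treatment discontinuation criteria: the AKI criterion starts at stage 2 and is not met. Again this shows breadth, not conflict.
4. **Stage 2 or 3 AKI judged possibly oxalate-related.** Treatment discontinuation criteria: the drug stops and unblinding is discretionary. Randomization and blinding: unblinding is mandatory only if the AKI counts as unexplained, and an injury attributed to oxalate arguably does not. The overlap is partial.

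The contradiction therefore rests on case 1, and cases 2 and 3 show the missing threshold. The reference to GCP procedures governs how a code is broken; it does not make a mandatory verb optional. Nor do the sections agree on who decides. One has two principal investigators evaluate the event after notification, with unblinding already required. The other leaves unblinding to the attending physician.

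**Route to the primary outcome.** For a code-break to change OSFD, four things must all happen: the allocation reaches someone who influences renal support; that person departs from the protocol-driven targets; the patient survives to day 14 (otherwise OSFD is 0 regardless); and on the affected day the patient is free of both vasoactive drugs and ventilation. The documents give no rate for any of these steps, nor for crystals or AKI by arm, so no size can be calculated.

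**The case against.** The strongest reply is that this is a difference of one verb in a condensed article. Detailed code-break procedures usually sit in the full protocol, the clean overlap is narrow, and in that overlap the allocation may well matter to care. A low unblinding threshold is also a defensible safety choice at an escalated dose of 500 mg/kg/day. Part of this stands: the overlap is narrow, and the sections can be harmonised with little text. But the point is not that detail is missing. Two stated rules disagree, and the safety argument does not need automatic unblinding, because the listed events already stop the drug whatever the allocation and the code remains available.

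Two stronger readings are tempting and are not supported.

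- Because crystals are listed as an adverse event and "Both AEs and SAEs will be evaluated at 8:00 a.m. every day", a reader might infer that the mandatory trigger is sought daily in every treated patient. The schedule in Table 1 lists no urinalysis. The safety section mentions urine tests without a timetable. The text on adverse events also has the investigator record an abnormal laboratory result only if it is clinically significant and not part of the underlying illness. Incidental crystals may thus be screened out.
- A reader might infer that the primary comparison is biased. Organ support is described as protocol-driven, no passage says who receives the allocation, and a changed renal support decision alters OSFD only in a 14-day survivor who needs no other support that day. Data extraction by blinded staff protects the recording of support rather than the decision to give it, so the risk is reduced but not removed. It remains a possibility, not a demonstrated effect.

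**Conclusion.** The concern holds as an inconsistency in the current text: mandatory unblinding with no crystal count or AKI stage in one section, discretionary unblinding for overlapping and graver events in another, and no statement of precedence. It should be corrected, because following the mandatory rule as written would break the code without asking whether the allocation affects care, for a finding that the protocol links to the active drug.

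The consequence is of unknown size. That crystals would occur more often under HDIVC is an assumption drawn from the protocol's own safety concerns; the documents report no rates. The effect on OSFD cannot be derived and may be small or zero. Confidence is high that the texts conflict and only moderate that the conflict matters in practice.

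**What to change.** In Randomization and blinding, replace the mandatory instruction with the rule already in Treatment discontinuation criteria. When one of the listed criteria is met, stop the study drug with the blind kept, and break the code only when the attending physician judges that knowing the allocation is needed for the patient's care. Keep immediate notification of both principal investigators and reporting to the review board. Report code-breaks by arm with the reason for each.

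The cost is a small amendment with ethics review, and retraining of sites, since the article reports central training as complete. Allocation would be disclosed slightly less automatically after a renal complication; the mandatory drug stop and access to the code do not change. The timing is favorable: the article reports 34 patients, all from the lead center, with the other centers still being activated, so most sites could start under one rule.
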